**Methods:**

A total of *N* = 162 children (5–12 years) with ADHD will be randomized to either an ED or a healthy diet. A comparator arm including *N* = 60 children being solely treated with CAU (e.g. medication) is used to compare the effects found in both dietary groups. The two armed RCT is performed in two youth psychiatry centers in the Netherlands, with randomization within each participating center. The primary outcome measure is response to treatment defined as a ≥ 30% reduction on an ADHD DSM-5 rating scale (SWAN) and/or on an emotion dysregulation rating scale (SDQ: dysregulation profile). This is assessed after 5 weeks of dietary treatment, after which participants continue the diet or not. Secondary outcome measures include the Disruptive Behavior Diagnostic Observational Schedule (DB-DOS), parent and teacher ratings of comorbid symptoms, cognitive assessment (e.g. executive functions), school functioning, physical measurements (e.g. weight), motor activity, sleep pattern, food consumption, nutritional quality of the diet, adherence, parental wellbeing, use of health care resources and cost-effectiveness. Assessments take place at the start of the study (T0), after five weeks (T1), four months (T2), eight months (T3) and 12 months of treatment (T4). T0, T1 and T4 assessments take place at one of the psychiatric centers. T2 and T3 assessments consist of filling out online questionnaires by the parents only.

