#### Primary outcome

##### Respondership

Parents and teachers are invited to rate the child’s ADHD traits using the SWAN questionnaire. The SWAN consists of 18 DSM-IV-based items scored on a 7-point Likert scale ranging from 3 (*far below average*) to -3 (*far above average*) with higher scores reflecting more severe ADHD symptoms [21]. Items 1 to 9 assess symptoms of the ADHD inattentive type and items 10 to 18 assess symptoms of the ADHD hyperactive/impulsive type. The Dutch version of the SWAN questionnaire is a reliable instrument (Cronbach’s α = .87) [28, 29] and demonstrates adequate convergent and discriminant validity [28, 29]. Parents and teachers also are asked to fill out the Strengths and Difficulties Questionnaire (SDQ) to assess emotion dysregulation [30]. The SDQ Dysregulation Profile (SDQ-DP) includes fifteen items representing emotional symptoms, conduct problems and hyperactivity-inattention [31]. The items can be answered on a 3-point scale ranging from 0 (*not true*) to 2 (*definitely true*) with higher scores indicating more emotion dysregulation problems. The Dutch version of the SDQ-DP demonstrates adequate reliability (Cronbach’s α = .85) and construct and longitudinal validity [31].

To align with the evaluation of the diet after 5 weeks, response to treatment will be evaluated by assessing the change in ADHD and emotion dysregulation symptoms at T0 and T1 or T4 (i.e. SWAN inattentive scale, SWAN hyperactive/impulsive scale and SDQ dysregulation profile rated by both parent and teacher: together six scales) [32]. A 30% or more symptom decrease will be regarded as a significant response to treatment (i.e. positive value), and a 30% or more symptom increase is regarded as significant deterioration of symptoms (i.e. negative value) [9, 33]. The primary outcome variable ‘respondership’ is divided into five categories:
Full responder (significant response on both parent and teacher rated scales): all scales are ≥ − 20% AND at least one of three parent rated scales shows a ≥ 30% symptom reduction AND at least one of three teacher rated scales shows a ≥ 30% symptom reduction.Partial responder (significant response on parent or teacher rated scale):

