### Sample size and power

The justification of sample size is calculated based on the assumption of superiority: we assume that the ED is more effective than the healthy diet on the ordinal primary outcome respondership (i.e. five categories: full responder, partial responder, mixed responder, non-responder and deterioration). A clinically relevant outcome is defined as detecting twice as many full responders in the ED group than in the healthy diet group. Each dietary group includes 81 children. With this sample size and using ordinal regression, the power is 0.99 (α = 0.05, two sided test) to detect double the amount of full responders in the ED compared with the HD (Table 4: scenario 1). In addition, the power to detect one and a half times as many full responders in the ED compared with the healthy diet is 0.64 (α = 0.05, two sided test) (Table 4: scenario 2).

**Table 4 Tab4:** Hypothetical Distribution of Participants for Power Calculation

	Full responder	Partial responder	Mixed responder	Non-responder	Deterioration
Scenario 1					
Elimination diet	16 (20)	45 (55)	10 (12%)	6 (8%)	4 (5%)
Healthy diet	8 (10%)	24 (30%)	21 (25%)	16 (20%)	12 (15%)
Scenario 2					
Elimination diet	12 (15%)	37 (45%)	13 (16%)	11 (14%)	8 (10%)
Healthy diet	8 (10%)	24 (30%)	21 (25%)	16 (20%)	12 (15%)

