### Statistical analyses

All primary analyses will be Intention To Treat. The primary outcome will be measured as an ordinal variable with five categories. Therefore, the effect of the intervention will be measured in terms of odds ratio, comparing odds for reducing ADHD symptoms and emotion dysregulation symptoms in the elimination diet group with the corresponding odds in the healthy diet group. Multiple logistic regression analyses will performed to compute the odds ratio and 95% confidence intervals, using ordinal logistic regression analysis. The CAU group will be used as a reference group.

Differences in continuous outcome measures between the dietary trajectories will be determined with analyses of ANCOVA. The follow-up value (T1, after five weeks) will be added as the dependent variable and the baseline value will be added as covariate. The two dietary groups will be compared on all outcomes at T1, using T0 scores as covariates. Clinical significance will be estimated using the partial eta squared effect. The CAU group will be used as a reference group.

In addition, a repeated measures ANOVA will be performed. First, the whole sample will be used (Intention to Treat) to determine whether adding a dietary treatment has beneficial outcomes on costs and effects of the whole treatment trajectory after 12 months (regardless of continuing the dietary treatment after 5 weeks or not). Next, per-protocol and post-hoc analyses will be performed using repeated measures ANOVA where the main outcome measures will be compared across the three conditions (i.e. elimination diet; healthy diet; CAU). Also, we will determine how many children adhered to the diet after 12 months, whether the intervention effects maintained after 12 months, which products are eliminated from the diet after 12 months and the nutritional quality of the attained diet after 12 months.

Finally, two moderator analyses will be performed: one comparing dietary responders versus non-responders (predicting respondership) and another comparing children/families adhering to a dietary treatment versus children/families that are not able to do so (predicting adherence). Both moderator analyses will be performed to compare children/families after 5 weeks and after 1 year of treatment.

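### Partial eta squared is named as the measure of clinical significance for the continuous T1 outcomes, but it is an unsigned share of residual variance that refers to no clinical scale

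*Protocol article*

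**What the plan says.** The Statistical analyses section of the protocol article treats the ordinal primary outcome and the continuous outcomes separately. On the latter it says: "Differences in continuous outcome measures between the dietary trajectories will be determined with analyses of ANCOVA". The T1 value is the dependent variable and the T0 value the covariate. The contrast is between the diets: "The two dietary groups will be compared on all outcomes at T1, using T0 scores as covariates". The measure of clinical importance follows directly: "Clinical significance will be estimated using the partial eta squared effect". No cut-off for partial eta squared, no difference in scale points and no adjusted mean difference with confidence interval is named as the basis for that judgement.

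Clinical criteria do appear elsewhere, but only for the primary outcome. Under Respondership: "A 30% or more symptom decrease will be regarded as a significant response to treatment", with an increase of the same size counted as deterioration. Under Sample size and power, a doubling of full responders is called clinically relevant. Neither criterion is linked to the ANCOVA outcomes.

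**The concern.** Clinical significance asks whether a difference is in the right direction and large enough to matter on a scale that clinicians understand. Partial eta squared answers another question: what share of the variance left after the baseline covariate is associated with group. Used as the protocol describes, it has three defects:

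- It adds nothing clinical to the ANCOVA test, because at fixed degrees of freedom it is a function of F alone.
- It treats benefit and harm of equal size alike, although the protocol's own response rule separates them.
- It rewards outcomes whose T0 and T1 scores correlate strongly, so a ranking of outcomes would partly rank stability of measurement.

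What is at stake is the clinical reading of the continuous T1 outcomes, such as cognition, motor activity and sleep. It would also cover the DB-DOS, whose raters are blinded to allocation, where that is analysed as a continuous score. This is a positive statement of the wrong quantity, so it is not a detail that a statistical analysis plan could be expected to supply.

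**Working it through.** **Inputs from the protocol article.** From Sample size and power: "Each dietary group includes 81 children", so N = 162. With an intercept, one covariate and one group term, the error degrees of freedom are 162 − 3 = 159 and the numerator degrees of freedom are 1.

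**Inputs assumed.** The T0-T1 correlation r is not given, so ranges are shown. The difference d is in within-arm SD units of the T1 score; 0.3 and 0.5 are illustrations.

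**The plan's own figures.** The article gives no figure for partial eta squared. Its power figures for the ordinal outcome are 0.99 and 0.64. A simulation of the tie-corrected Wilcoxon test on the Table 4 counts (20,000 runs, 81 per arm, two-sided α = 0.05) gives 0.995 and 0.643. This confirms the reading of the sample size and says nothing further on this point.

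**Step 1: relation to the p-value.** Partial eta squared = F·df1/(F·df1 + df2), here F/(F + 159). The two-sided 5% critical value is F = 3.90, and 3.90/(3.90 + 159) = 0.024. Every p-value maps to one value of partial eta squared, and the reverse.

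**Step 2: sign.** With 1:1 allocation the population value is

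(d²/4) / (d²/4 + 1 − r²).

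Because d enters as a square, +d and −d give the same result. In simulated ANCOVAs with 81 per arm and r = 0.5, differences of −0.5 SD and +0.5 SD gave means of 0.083 and 0.082, equal within simulation error.

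**Step 3: dependence on r.** For d = 0.3, d²/4 = 0.0225:

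| r | 1 − r² | Partial eta squared |
|---|---|---|
| 0.3 | 0.91 | 0.0225/0.9325 = 0.024 |
| 0.4 | 0.84 | 0.0225/0.8625 = 0.026 |
| 0.5 | 0.75 | 0.0225/0.7725 = 0.029 |
| 0.7 | 0.51 | 0.0225/0.5325 = 0.042 |
| 0.8 | 0.36 | 0.0225/0.3825 = 0.059 |
| 0.9 | 0.19 | 0.0225/0.2125 = 0.106 |

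The ratio is 1.5 over r = 0.5 to 0.7, 2.3 over 0.4 to 0.8, and 4.4 over 0.3 to 0.9. For d = 0.5 the value runs from 0.064 (r = 0.3) to 0.248 (r = 0.9).

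**Step 4: the same relation inverted.** From the formula, d = 2·√[η/(1 − η)·(1 − r²)], with η for partial eta squared. At η = 0.0239, η/(1 − η) = 0.0245. At r = 0.4, d = 2·√(0.0245 × 0.84) = 0.29 SD. At r = 0.8, d = 2·√(0.0245 × 0.36) = 0.19 SD. One reported value thus stands for different differences on different scales.

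**The case against.** The case for leaving the sentence alone is that it puts a loose label on an ordinary effect size for outcomes that do not decide the trial. Much of that stands. The primary outcome has a signed 30% rule, a deterioration category and an odds ratio with 95% CI, and the parent- and teacher-rated SWAN and SDQ dysregulation scales are judged there. None of this is touched.

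Several stronger conclusions are tempting, and the document does not support them.

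- A reader might infer that harm could pass for benefit. The adjusted means come from the same ANCOVA and show the direction.
- A reader might infer that partial eta squared ignores the size of the difference. Within one outcome, with sample size and residual variance fixed, it rises with the absolute difference.
- A reader might infer that many null outcomes would be called clinically significant, because the quantity is positive when the diets are identical. The mean under no effect is only 1/160 = 0.006, and the plan sets no cut-off. Any such rate depends on the cut chosen: about 21% of null outcomes exceed 0.01, but 0.17% exceed 0.06.
- A reader might infer, from the remark that care as usual serves as reference group, that the figure would pool three groups. The section says that the two diets are compared, which is a single contrast.

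The fourfold variation also needs the extremes of the assumed correlation range; over 0.5 to 0.7 it is 1.5-fold.

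What the objection does not answer is the label itself. The text does not offer partial eta squared as a descriptive effect size. It names it as the estimate of clinical significance.

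**Conclusion.** The point holds for the continuous ANCOVA outcomes at T1. Partial eta squared cannot support a statement of clinical significance, because for this contrast it repeats the test result (0.024 at p = 0.05), carries no sign and has no clinical reference. Nor can it be compared across scales on clinical terms: a fixed 0.3 SD difference gives 0.026 to 0.059 for r between 0.4 and 0.8, and 0.024 to 0.106 for r between 0.3 and 0.9.

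The algebra in steps 1 and 2 rests only on the planned model and sample size. The sizes in steps 3 and 4 rest on assumed correlations and differences, and on equal within-arm variances. The primary analysis and its conclusion are unaffected. The sentence should be corrected because it fixes a wrong rule, but it does not threaten the trial's main result.

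**What to change.** Replace the sentence. For each continuous outcome, report the baseline-adjusted mean difference (elimination diet minus healthy diet) with its 95% CI, in scale points and in T0 SD units. Judge clinical relevance from the direction of that difference and its CI against an important difference prespecified for the scale, where one exists; where none exists, report the estimate without a claim of clinical significance. Keep partial eta squared, if wanted, only as a description of variance explained.

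Do not turn the 30% rule into a between-arm difference in points. It is a percentage change within a child, and because SWAN items run from 3 to −3 such a percentage has no fixed value in points. For the SWAN and SDQ dysregulation scales that criterion is already applied through respondership.

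The cost is a short change of wording, plus the choice of important differences before the data are analysed. The adjusted difference and its CI come from the ANCOVA already planned, so no new data, sample or model is needed.

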To address these issues, the ‘Treatment of ADHD with Care as usual versus an Elimination diet’ (TRACE) study has been developed. This is the first RCT (two armed, 50:50 ratio) to determine the short- and long-term effectiveness and cost-effectiveness of an ED compared to an active control group (a healthy diet). Care As Usual (CAU) is included as a comparator arm. During the initial 5 weeks of the study, participants receiving a dietary treatment are not allowed to start any other treatment. Also, medication prior to the dietary treatment has to be discontinued no later than 1 week before start of the diet. The study will examine effects on both ADHD and emotion dysregulation, given that an ED showed equal effects on ADHD and its common comorbidity Oppositional Defiant Disorder (ODD) (i.e. children with ODD are more likely to experience emotion dysregulation problems) [14]. We will substantially improve upon previous studies by comparing an ED with a healthy diet (based on the World Health Organization (WHO) guidelines), comparing the two dietary treatments with CAU, examining the short- and long-term effects (i.e. after 5 weeks and 1 year) and cost-effectiveness, measuring the nutritional quality of the consumed diets and including blinded and objective measurements.

The primary objective of the TRACE study is to quantify the short-term (after 5 weeks) effectiveness in reducing ADHD and emotion dysregulation symptoms of an ED compared to an active control group (a healthy diet) in children aged 5–12 years with ADHD: we assume that the ED is more effective than the healthy diet. Secondary, the study aims at examining the long-term (after 1 year) effects in reducing ADHD and emotion dysregulation symptoms. Moreover, the study aims at examining the short- and long-term effects of an ED compared to an active control group (a healthy diet) in reducing secondary outcome measures related to ADHD such as cognitive outcomes, motor activity and sleep pattern. In addition, the study aims to identify potential moderators and mediators (e.g. socioeconomic status (SES), ethnicity, comorbidity) of the short- and long-term response to dietary treatments, and to examine the nutritional quality of the attained diet and health of children treated with a dietary treatment compared to CAU. Finally, the study aims to examine the cost-effectiveness of the dietary treatments compared with CAU.

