### Procedures

Families who are interested to participate in the TRACE study are informed via telephone and information letters (sent via e-mail). Families can choose whether they want to participate in the dietary treatment arms or the CAU arm. If they choose a dietary treatment, they will be randomly assigned to either the elimination diet or the healthy diet.

If the eligibility criteria are met, parents are invited for an intake with a researcher to explain further details of participation, plan appointments and to disclose which diet the child is randomized to via a sealed envelope. Both parents fill out a written informed consent for the TRACE study (Additional file 1). If children are 12 years old, they also need to sign the consent forms. In addition, teachers are informed about the study via e-mail and general practitioners via postal letters.

Assessments will take place at baseline (T0), after five weeks of treatment (T1), after four (T2), eight (T3) and 12 (T4) months after start of treatment (i.e. dietary treatment or CAU). T0 will be scheduled within two weeks prior to the start of the treatment. Medication treatment prior to the dietary treatment has to be discontinued no later than one week before start of the diet. T0, T1 and T4 assessments will take place at one of the two participating sites. For the T2 and T3 assessments, parents are asked to fill out questionnaires online. Teachers are asked to fill out online questionnaires at T0, T1 and T4. Figure 1 depicts a flowchart on recruitment and procedure of the study.

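### For continuous outcomes the plan names no ED versus healthy diet test at 12 months, only a repeated measures ANOVA whose omnibus group tests, if T1 is included, do not test a T4 difference

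*Protocol article*

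**What the plan says.** The Background section sets a time-point objective: "Secondary, the study aims at examining the long-term (after 1 year) effects in reducing ADHD and emotion dysregulation symptoms".

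The Statistical analyses section treats the two horizons differently for continuous outcomes.

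- **Five weeks.** The method and visit are fixed: "The two dietary groups will be compared on all outcomes at T1, using T0 scores as covariates".
- **Twelve months.** The text reads "In addition, a repeated measures ANOVA will be performed". Its first use is by intention to treat, to judge costs and "effects of the whole treatment trajectory after 12 months (regardless of continuing the dietary treatment after 5 weeks or not". Then "per-protocol and post-hoc analyses will be performed using repeated measures ANOVA where the main outcome measures will be compared across the three conditions".
- **Maintenance.** The authors will also determine "whether the intervention effects maintained after 12 months". No method is attached.

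Two other places bear on the point. Under Respondership, the ordinal outcome is evaluated by "assessing the change in ADHD and emotion dysregulation symptoms at T0 and T1 or T4", so a T4 version exists. Under Procedures, "Teachers are asked to fill out online questionnaires at T0, T1 and T4". Table 3 gives the same three visits for the DB-DOS, the comorbidity ratings, COTAPP and actigraphy.

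**The concern.** Whether the arms differ at one year is a question about T4. A repeated measures ANOVA offers two omnibus group tests. The null of group-by-time is that the arms have the same profile over all visits entered. The null of the group main effect is that they have the same mean over all those visits, T0 included. Once T1 is entered, neither is the null of no T4 difference.

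This matters here because the plan expects a T1 difference in favour of the ED, and after five weeks families may leave the diet for care as usual (CAU). A gap that opens by T1 and closes by T4 is therefore a realistic course. The omnibus tests could then be significant on account of T1 alone. In the three-condition version they could also be significant because the non-randomized CAU group differs at T1, even if the two diets never differ. At stake are the 12-month results on the continuous outcomes and the statement on maintenance, which currently has no test of its own.

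**Working it through.** **1. The plan's own power figures.** A proportional-odds model fitted to the Table 4 counts gives OR 3.73 (scenario 1) and 1.96 (scenario 2). The Whitehead formula is power = Φ(|log OR|·√V − 1.96), with V = n₁n₂/(3N)·(1 − Σp̄³). It gives 0.996 and 0.661. Simulation with the Wilcoxon test gives 0.994 and 0.639. The stated 0.99 and 0.64 reproduce.

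**2. Effect sizes.** With d = log(OR)·√3/π, OR 1.96 gives 0.37 SD and OR 3.73 gives 0.725 SD. These serve only as a scale for plausible T1 effects on a continuous outcome; the documents give none.

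**3. Assumptions.** 81 per arm and two-sided α = 0.05 are from Sample size and power. Visits T0, T1, T4 follow Table 3. The documents give no SD or between-visit correlation, so I take SD 1, equal correlation ρ from 0.3 to 0.8, and no missing data.

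**4. Formulas**, for arm differences δ at the three visits:

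- Group-by-time: F on 2 and 320 df, noncentrality λ = (81/2)·Σ(δ − δ̄)²/(1 − ρ).
- Group main effect: t on 160 df, noncentrality δ̄/√[(2/81)(1 + 2ρ)/3].
- T4 ANCOVA: t on 159 df, noncentrality δ_T4/√[(2/81)(1 − ρ²)].

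**5. Effect at T1 only, δ = (0, d, 0).** Here Σ(δ − δ̄)² = d²(1/9 + 4/9 + 1/9) = 2d²/3, so λ = 27d²/(1 − ρ). For d = 0.37 and ρ = 0.5, λ = 27 × 0.1369/0.5 = 7.39. The group-term noncentrality is 0.1233/0.1283 = 0.961. Rejection rates:

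| d at T1 | ρ | Group-by-time | Group main effect | T4 ANCOVA |
|---|---|---|---|---|
| 0.37 | 0.3 | 0.523 | 0.188 | 0.05 |
| 0.37 | 0.5 | 0.677 | 0.159 | 0.05 |
| 0.37 | 0.7 | 0.889 | 0.141 | 0.05 |
| 0.37 | 0.8 | 0.977 | 0.134 | 0.05 |
| 0.725 | 0.3 | 0.986 | 0.553 | 0.05 |
| 0.725 | 0.5 | 0.999 | 0.465 | 0.05 |
| 0.725 | 0.7 | 1.000 | 0.401 | 0.05 |
| 0.725 | 0.8 | 1.000 | 0.375 | 0.05 |

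Simulation (4,000 trials per cell, ρ 0.3 to 0.7, Greenhouse-Geisser correction) agrees: 0.51 to 0.89 and 0.985 to 1.00 for group-by-time, and 0.04 to 0.06 for the T4 ANCOVA. With all five visits, group-by-time rejects in 0.48 to 0.89 and 0.986 to 1.00, and the main effect in 0.08 to 0.11 and 0.19 to 0.28. With three groups (81/81/60), group-by-time rejects in 0.51 to 0.90 and 0.99 to 1.00. For smaller T1 effects, simulated group-by-time rejection is 0.17 to 0.36 at 0.2 SD and 0.38 to 0.72 at 0.3 SD.

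**6. Sustained effect, δ = (0, d, d).** Now Σ(δ − δ̄)² = d²(4/9 + 1/9 + 1/9) = 2d²/3, the same value as in step 5. Under these assumptions the three-visit group-by-time test rejects exactly as often for an effect that has vanished by T4 as for one that has lasted, so its P value cannot tell the two apart. Power at ρ = 0.4/0.6/0.8:

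| Test | 0.35 SD | 0.5 SD |
|---|---|---|
| Group main effect | 48/41/35% | 78/69/62% |
| Group-by-time, T0/T1/T4 | 54/73/96% | 86/96/100% |
| Group-by-time, T0/T4 only | 52/70/94% | 82/94/100% |
| T4 ANCOVA | 68/79/96% | 93/98/100% |

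The T0/T4 row is the change-score test, with noncentrality d/√[(2/81)·2(1 − ρ)].

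**The case against.** The strongest reply is that the article does not specify the analysis criticised here. It fixes no visits, no term and no contrast, and a full protocol or analysis plan may do so. Run on T0 and T4 only, the group-by-time term is the test of the difference in change to 12 months, which is valid at 5%. This stands, and it makes the error rates conditional on T1 being entered. It does not remove the point: the article did choose a method for 12 months, framed it around the treatment course as a whole, and gave T4 no counterpart to its T1 ANCOVA. Even against the T0/T4 reading, the T4 ANCOVA has more power at low correlation (68 v 52% for 0.35 SD at ρ = 0.4), with almost none to gain at ρ = 0.8.

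A reader might infer that the whole one-year objective rests on the ANOVA. The documents do not support that. Respondership is defined at T4, and the ordinal regression is not restricted to T1, so the symptom objective may have its own T4 comparison.

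A reader might also infer that a vanished effect will usually be reported as a 12-month effect. That predicts how results will be read. A significant interaction is normally followed by a look at the time points, post-hoc analyses are mentioned, and maintenance is listed as a separate question. Nor does a majority rejection rate hold in general for the main effect, whose rates are mostly below one half.

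The power loss is large only if the main effect is the test; under group-by-time it is small to moderate. Finally, the intention-to-treat ANOVA asks whether adding a diet helps over the trajectory, which reads as diet versus CAU. An ED versus healthy diet contrast at T4 is therefore an addition to that analysis and does not replace it.

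**Conclusion.** The point holds for the continuous outcomes and for the maintenance statement. The 5-week comparison is pinned to a visit and adjusted for baseline; the 12-month comparison is not. If T1 enters the ANOVA and the true T4 difference is zero, group-by-time rejects in about 52 to 100% of trials and the group main effect in about 13 to 55%, for T1-only effects of 0.37 to 0.725 SD on three visits. If the main effect is the test, power for a sustained 0.35 SD difference is about 35 to 48%, against 68 to 96% for a T4 ANCOVA. These figures rest on assumed correlations, equal variances, complete data and an odds-ratio-to-SD conversion that the documents do not supply. That neither omnibus null is a T4 null does not depend on them. This is a secondary objective, and the primary 5-week analysis is untouched.

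**What to change.** - Add, as the 12-month test for continuous outcomes, the ED versus healthy diet difference at T4 from an ANCOVA of the T4 value on the T0 value, as already planned for T1. The T4 contrast from a mixed model with T0 as covariate would serve equally.
- Report maintenance as two estimates with 95% confidence intervals: the T4 difference, and the change in that difference from T1 to T4.
- Compare 12-month costs on the accumulated total already defined in the cost-effectiveness paragraph. Table 3 lists no T0 cost measurement, and a single total has no repeated measure to analyse.
- Keep the repeated measures ANOVA, including the comparison with CAU, as a description of the trajectory, and draw no 12-month conclusion from its omnibus terms.

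The cost is a few sentences in the analysis section. Data, visits and sample size stay the same.
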